### Framework

The hypothesis framework is one of non-inferiority with inference at the individual level. A number of endpoints with limited numbers of events will be analysed without a non-inferiority framework and interpretation will be based only on a point estimate and confidence interval for the effect measure. For the analysis of VT pneumococcal carriage in year 2, we specify a superiority framework to test for potential early impact of the alternative schedule.

### Interim analyses and stopping guidance

#### Interim analyses

No interim analyses are planned. Analysis of the endpoint of VT prevalence in children with clinical pneumonia in year 2 will be conducted to provide information for the funding agencies and neither the investigators nor Trial Steering Committee (TSC) will be aware of the results. The Data Monitoring Committee (DMC) will be aware of the results. The aim of the year 2 analysis is to identify potential early differential effects between the two groups. Given that no interim analyses are planned, there are no planned adjustments to the significance level due to interim analyses.

#### Guidance for stopping the trial early

The trial may be stopped early if there is evidence that the risk of pneumococcal disease is greater in one compared to the other trial group. Examples of such findings are group-wise differences in the incidence of VT IPD, radiological pneumonia, or hospitalisation. Although the correlation between the prevalence of VT carriage and disease risk is unclear, and carriage is not a measure of disease risk, the DMC may also gain appreciation of trial safety from the measures of VT carriage in children with clinical pneumonia and in community surveys. Rather than specify a formal stopping rule, the DMC will regularly view the accruing data, considering the overall pattern of results, including the consistency of any effects, the potential for effects to change over time, particularly the accumulation of indirect effects over time [17], and the potential for cluster-specific events of a temporal nature.

If the DMC recommends that the trial be stopped early, a joint meeting of the DMC, TSC, and Central Stakeholder Committee will make a recommendation to the Sponsor regarding post-trial procedures, including whether a dose of PCV be administered to children in a group found to be inferior.

### Timing of analyses

#### Timing of analysis of year 2 data

The analysis of year 2 data on VT prevalence in children with clinical pneumonia will be conducted in year 3, following the approval of the statistical analysis plan (SAP) by the DMC and TSC, and following submission of the SAP for publication. The results of this analysis will be concealed from the investigators and TSC but available to the DMC and funding agencies.

#### Timing of final analyses

Final analyses will be conducted at one point in time but presented in two manuscripts, one including the primary and secondary endpoints and a second including the tertiary endpoints.

### Timing of outcome assessments

#### Timing of primary endpoint assessment

The primary outcome of VT carriage in children with clinical pneumonia is measured continuously throughout the course of the trial among resident children presenting unwell to health facilities in the trial area. That is, the outcome is assessed whenever a resident child presents unwell to a health facility, at any age between 2 and 260 weeks. This outcome will be presented as prevalence at four time points measured using data collected during each of the 4 years of intervention. The primary endpoint will be analysed using data from year 4 of intervention, following the greatest observable accumulation of the effects of the two schedules. Based on the number of patients with clinical pneumonia enrolled after elapse of 11 months in year 4, the 12-month period may be extended by 1–2 months to achieve the required sample size. Table 2 shows the results of the relative impact of the alternative versus standard schedule on VT carriage prevalence in children with clinical pneumonia.

**Table 2 Tab2:** Results of vaccine schedule impact on the prevalence of vaccine-type pneumococcal carriage in children aged 2–260 weeks with clinical pneumonia

	Alternative schedule			Standard schedule			Adjusted prevalence ratio (95% CI)
	Number VT *Spn*	Number measured	Prevalence % (95% CI)	Number VT *Spn*	Number measured	Prevalence (95% CI)	
Year 1	n	N	n/N ()	n	N	n/N ()	x.y (95% CI)
Year 2	n	N	n/N ()	n	N	n/N ()	x.y (95% CI)
Year 3	n	N	n/N ()	n	N	n/N ()	x.y (95% CI)
Year 4	n	N	n/N ()	n	N	n/N()	x.y (95% CI)
^a^Age (weeks)							
2–12	n	N	n/N ()	n	N	n/N ()	x.y (95% CI)
13–40	n	N	n/N ()	n	N	n/N ()	x.y (95% CI)
41–104	n	N	n/N ()	n	N	n/N ()	x.y (95% CI)
105–260	n	N	n/N ()	n	N	n/N ()	x.y (95% CI)

^a^Age-stratified analyses in year 4

#### Timing of secondary endpoint assessments

The secondary endpoint of VT pneumococcal carriage prevalence among all ages in the population will be assessed in year 3 (tertiary endpoint) and year 4 (secondary endpoint) of the trial. Radiological pneumonia is measured during continuous population-based clinical surveillance and analysis will include all events in children enrolled to receive the intervention.

#### Timing of tertiary endpoint and disease endpoint assessment

The tertiary endpoint of VT carriage in infants aged 6–12 weeks who have not yet received their first dose of PCV will be assessed in year 4. Disease endpoints will be continuously measured in population-based clinical surveillance throughout the course of the trial. The disease endpoints will be assessed cumulatively during the 4 years of intervention and within each of the 4 years of intervention. The non-pneumococcal invasive bacterial disease endpoint is included as a control condition to detect potentially differential case ascertainment or access to care in the two groups. Supplementary Table 3 shows the results of disease endpoints in the trial.

## Statistical principles

### Confidence intervals and p-values

#### Level of statistical significance

The level of statistical significance for all non-inferiority hypotheses will be set at an α-level of 0.05 using two-sided significance tests [18, 19]. We specify a two-sided α-level of 0.05 as we wish to know the lower, as well as upper limit of the confidence interval around the effect estimates, as it is plausible that the alternative schedule may be superior to the standard schedule. For the superiority hypothesis concerning VT prevalence in children with clinical pneumonia in year 2, we will use a two-sided significance test with an α-level of 0.05.

#### Multiplicity

No adjustment will be made to the level of significance for multiple hypothesis tests. Hypothesis tests will be presented with a specific *p*-value for researchers to interpret within the context of all presented results and all the available evidence in the field [20].

#### Confidence intervals

Two-sided 95% confidence intervals will be used for all non-inferiority endpoints [18, 19] and the superiority analysis of VT prevalence in patients with clinical pneumonia endpoint in year 2. To account for the effect of clustering, 95% confidence intervals will be constructed using generalised estimating equations (GEE) with exchangeable correlation structure, based on individual-level data and a regression model using a log link function, binomial family, and robust standard errors. Confidence intervals for incidence rate ratio outcome measures will be calculated following specification of a cluster-level analysis using a negative binomial distribution. The negative binomial distribution allows an overdispersion parameter that accounts for clustering and repeated events, while cluster-level person-time will function as weights in the analysis. Confidence intervals for incidence rate ratios will be calculated by dividing and multiplying the point estimate by an error factor based on the *t*-distribution [21].

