#### Sample size calculation

Sample size calculations were based on the primary outcome of NP carriage of VT pneumococci in children aged 2–260 weeks with clinical pneumonia. Initial sample size calculations assumed an equal number of 60 participants measured for the primary endpoint in each cluster, that is, 2040 in each group and 4080 in total. Using Basse data from 2015, we assumed the prevalence of VT carriage to be 13% in both the standard and alternative schedule groups. The alternative schedule will be considered non-inferior if the upper limit of the two-sided 95% confidence interval for the prevalence ratio is ≤1.38 (0.18/0.13 = 1.38). Using Basse data, we estimated the intra-class correlation coefficient (ICC) to be 0.01–0.02. We calculated study power using the methods of Farrington et al. [15] and Donner et al. [16]. Using the more conservative value for ICC of 0.02, a minimum number measured for the primary endpoint per cluster of 60, with 34 clusters per arm (with design effect of 2.18) and *α*=0.05, a sample size of 2040 per arm will provide 93% power to test the non-inferiority of the alternative schedule.

To increase confidence in the study power, we simulated data using 2015 BHDSS data on cluster-wise VT carriage prevalence in children with pneumonia. The simulated data were designed to be similar to the villages included in this trial with respect to the mean carriage prevalence, as well as the variability in prevalence across clusters. Using 1000 simulated populations, each consisting of 68 clusters of 60 individuals, baseline prevalence of 10% and a largest acceptable increase of 4%, i.e. from 10% to 14% (i.e. non-inferiority prevalence ratio of 0.14/0.10=1.40), study power was ≥85% in most scenarios.

During the piloting of trial procedures, it became clear that the number of patients measured for the NP carriage endpoint would be quite variable among clusters with less than 60 patients in some clusters. Further simulations using local data on the variable numbers expected per cluster in 1 year (*N*=3948, median=33, range 7–506) and assuming VT prevalence of 16% in both groups demonstrated trial power of 90%. In order to maximise trial power, the primary outcome will be measured in all eligible patients in each of the 68 clusters with a total number ≥4080 included in the final year 4 analysis.

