#### Population-level primary endpoint

The primary analysis will be assessment of the impact of the two schedules on VT carriage prevalence in resident children aged 2–260 weeks with clinical pneumonia. Interpretation will relate to whether the prevalence of VT carriage in a child who lives in a geographic area allocated to the alternative schedule is not greater than the non-inferiority threshold when compared to a child who lives in a geographic area allocated to the standard schedule.

The primary endpoint will be calculated as the proportion (prevalence) of children with clinical pneumonia who have NP carriage of VT pneumococci. The contrast between the two groups will be presented as a prevalence ratio, with ratios expressed as the prevalence in the alternative compared to standard schedule group. To account for cluster-level non-independence, the primary analysis will use generalised estimating equations (GEE) with a log link, binomial family, and exchangeable correlation structure. The primary analysis GEE model will include the stratifying covariates used in the randomisation of clusters: (i) cluster location in BHDSS or FWHDSS, (ii) cluster high or low baseline incidence of clinical pneumonia. Analysis will not include the other variables used to restrict the randomisation lists to ensure balance in the other baseline characteristics (see the ‘Randomisation’ section) [27]. Patients and clusters will be analysed according to their random allocation.

If the ratio of VT prevalence in the two groups is given by ρ = π_1_ : π_0_, where *ρ* is the true ratio between the prevalence in the alternative (π_1_) and standard (π_0_) schedule groups, the null hypothesis is H_0_ : *ρ* > 1.38, and the alternative hypothesis is H_1_ : *ρ* ≤ 1.38. The null hypothesis represents inferiority of the alternative schedule [13]. Non-inferiority will be established if the upper limit of the confidence interval around the prevalence ratio is ≤1.38.

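### The primary GEE interval names no small-sample correction; with 68 clusters of very unequal expected size, false non-inferiority is about 3.3–4.1% rather than the nominal 2.5%

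*SAP article*

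**What the plan says.** All references are to the SAP article.

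- **Confidence intervals.** Prevalence-ratio intervals come from an individual-level GEE with exchangeable correlation, a "log link function, binomial family, and robust standard errors". No finite-sample correction or reference distribution is named. For incidence rate ratios the same section does specify an error factor from the t-distribution.
- **Level.** "Two-sided 95% confidence intervals will be used for all non-inferiority endpoints", and the level "will be set at an α-level of 0.05 using two-sided significance tests". The nominal chance of wrongly declaring non-inferiority is therefore 2.5%.
- **Population-level primary endpoint.** "Non-inferiority will be established if the upper limit of the confidence interval around the prevalence ratio is ≤1.38". The model holds treatment and the two stratifiers, so four parameters with the intercept.
- **Sample size calculation.** There are 68 clusters. Cluster sizes expected in one year total 3948, with "median=33, range 7–506".
- **Alternative methods.** A logit link with marginal standardisation and the delta method is used if the log-link model fails to converge. No variance correction is mentioned there either.
- **Sensitivity analyses.** None is planned.

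**The concern.** The plain sandwich variance uses each cluster's own residuals. A cluster with high leverage pulls the fit towards itself, so its residuals are too small and the variance is biased downwards. The bias fades as the number of clusters grows, but more slowly when sizes are very unequal. Sixty-eight clusters may seem ample; sizes from 7 to 506 make that less safe.

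The direction matters. In a non-inferiority test a short interval favours the new schedule, because the upper limit falls below the margin too often. The plan has no second analysis that would show this.

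**Working it through.** **Inputs from the SAP article.** 34 clusters per arm; sizes with total 3948, median 33, range 7–506 (mean 3948/68 = 58); "we estimated the intra-class correlation coefficient (ICC) to be 0.01–0.02"; VT prevalence 13% (analytic calculation) or 16% (variable-size simulation); margin 1.38; four-parameter model.

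**Assumed.** The shape of the size distribution between the published median and extremes, and small stratifier effects. The main shape has N = 3943 and a coefficient of variation (CV) of size of 1.29. Counts are beta-binomial. Allocation is stratified, with the two largest clusters in opposite arms and totals within 10%.

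**Rule tested.** Non-inferiority if log(PR) + q × SE ≤ log(1.38), where q = 1.96 with the plain robust SE is the plan as written.

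**Step 1: the plan's own figure.** At a true ratio of 1.0, VT 16% and ICC 0.01, the rule gives 89.9% power against the stated 90%. At ICC 0.02 it gives 79.7%. The plan states neither the ICC nor the interval used in its simulation, so the match is consistent with the plain interval but does not prove it was used.

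**Step 2: error at a true ratio of 1.38** (about 40,000 trials per row; Monte Carlo SE about 0.1 point).

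| VT, ICC | Empirical SD | Mean robust SE | Shortfall | Plain, z | Plain, t(64) | Kauermann-Carroll, t(64) | Mancl-DeRouen, t(64) |
|---|---|---|---|---|---|---|---|
| 13%, 0.01 | 0.1077 | 0.0987 | 8.4% | 3.99% | 3.74% | 3.10% | 2.53% |
| 13%, 0.02 | 0.1251 | 0.1167 | 6.7% | 3.62% | 3.36% | 2.88% | 2.44% |
| 16%, 0.01 | 0.0952 | 0.0871 | 8.5% | 4.05% | 3.77% | 3.21% | 2.56% |
| 16%, 0.02 | 0.1103 | 0.1030 | 6.6% | 3.66% | 3.41% | 2.90% | 2.40% |

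Two-sided coverage of the plain interval is 92.0–92.8%.

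**Step 3: plausibility by hand.** First row: 0.0987/0.1077 = 0.916, so the effective quantile is 1.96 × 0.916 = 1.80, with a normal tail of 3.6%. Second row: 0.1167/0.1251 = 0.933, giving 1.83 and 3.4%. The short SE therefore explains most of the excess. The remainder is in line with the robust SE itself varying between trials.

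**Step 4: dependence on the size distribution.**
- A log-normal shape with N = 3942, median 33 and range 7–506: 3.3–3.9%.
- Two town-sized clusters (506 and 450): 3.6–4.3%.
- CV 0.5–0.9, milder than the published range implies: 3.2–3.6%.
- Equal clusters of 60, as in the surveys: about 2.9–3.3%.

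**Step 5: power under the corrected interval.** With Mancl-DeRouen and t(64), at VT 16%, power goes from 89.9% to 85.8% at ICC 0.01 (4.1 points) and from 79.7% to 74.3% at ICC 0.02 (5.4 points).

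**The case against.** The best reply is that the article is silent rather than wrong. It neither names nor excludes a correction, and supplementary material exists. That stands as to wording: what can be said is that no correction is named. It does not dispose of the point. The article is the SAP, its section on intervals specifies the variance estimator, and it goes into t-based detail for rate ratios. A statistician following it as written would compute the plain interval.

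The excess is also modest, and it alters the conclusion only when the upper limit lies just under 1.38. That is accepted.

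A reader might infer more than the document supports:

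- **That a few clusters dominate.** The largest expected cluster holds 506/3948 = 13% of children, but exchangeable GEE weights it by n/(1 + (n − 1) × ICC). That is 506/6.05 = 84 at ICC 0.01 and 506/11.1 = 46 at ICC 0.02, about 3–4% of the total weight. Unequal size raises leverage; no cluster dominates.
- **That the t-distribution for rate ratios is an inconsistency.** Those ratios come from a separate cluster-level analysis, and a t quantile alone would not repair the GEE interval.
- **That the analytic 93% power is inflated by this.** That figure was calculated "with 34 clusters per arm (with design effect of 2.18"), not from a sandwich interval. Whether it is right is a separate matter.

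**Conclusion.** The point holds as a moderate flaw. As written, the primary interval does not deliver its stated level. False non-inferiority at the margin is about 3.3–4.1% against 2.5%, an absolute excess of roughly 0.8–1.6 points. This rests on reading the named robust standard errors as the plain sandwich with a normal quantile, on year 4 sizes resembling the planning figures, and on an assumed shape between the published median and extremes. The direction did not change under any shape tried, including equal clusters; only the size did. The excess in the community and infant surveys is under one point, so the primary-endpoint figures should not be carried over to them.

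**What to change.** Add one sentence to the section on confidence intervals: all prevalence-ratio GEE intervals, including those from the logit and delta-method fallback, use the Mancl-DeRouen bias-corrected sandwich variance with a t quantile on the number of clusters minus the number of cluster-level parameters (68 − 4 = 64 for the primary model).

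The choice of correction should be explicit. A t quantile on the plain SE leaves about 3.3–3.8%, and Kauermann-Carroll with t leaves about 3%; only Mancl-DeRouen with t brought the error back to about 2.5%.

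Restate the simulated 90% power for variable cluster sizes under this interval, giving the ICC used. The cost is about 4–6 points of power in that simulation, for example from about 90% to 84–86% at VT 16% and ICC 0.01. Existing software suffices and data collection is unaffected. The change should be fixed before the final analysis.

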### Adherence and protocol deviations

#### Definition and assessment of adherence to the intervention

##### Vaccination status—per-protocol

Vaccination per-protocol (PP) will be defined as a child enrolled into the study at ≤273 days (≤40 weeks) of age and who received the allocated schedule of PCV doses during follow-up. PP administration of the standard schedule of three doses will require allocation to the standard schedule and administration of three doses of PCV at ≤152 days (≤22 weeks) of age. PP administration of the alternative schedule will require administration of two doses of PCV, the first dose ≤152 days (≤22 weeks) of age, and administration of the second dose ≥273 days (≥40 weeks) and ≤365 days (≤52 weeks) of age.

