#### Definition of protocol deviations

Table 4 defines the protocol deviations in the trial. Enrolment of ineligible participants occurs when non-residents or infants greater than the age limit are enrolled. Incorrect administration of PCV doses occurs when infants enrolled in the alternative schedule group receive a second or third dose of PCV before 40 weeks of age, and in the standard schedule group if the third dose is administered after 40 weeks of age.

**Table 4 Tab4:** Definition of protocol deviations

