**Reason for protocol deviation**	
Enrolment of ineligible participant	Age >40 weeks on day of consent Non-resident on day of consent
Enrolment without consent	Enrolled without valid consent form

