**Non-adherence to vaccine schedule**	
Incorrect dose given	
Standard schedule—received >3 doses	
Standard schedule—3rd dose age >40 weeks	
Alternative schedule—2nd dose age <40 weeks	
Alternative schedule—3rd dose age <40 weeks	
Ineligible and received alternative schedule	Non-resident—2nd dose age ≥36 weeks
Withdrawn and received alternative schedule	Withdrawn—2nd dose age ≥36 weeks

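### The per-protocol definition equates 273 days with 40 weeks (it is 39), and the dose-deviation rules reuse 40 weeks with no day value, so an on-time booster can be both per-protocol and a deviation

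*SAP article*

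**What the plan says.** The SAP section *Vaccination status—per-protocol* uses the same pair of units twice. A per-protocol child must be "enrolled into the study at ≤273 days (≤40 weeks) of age", and for the alternative schedule the booster criterion is "administration of the second dose ≥273 days (≥40 weeks) and ≤365 days (≤52 weeks) of age".

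The section *Definition of protocol deviations* and Table 4 take up the 40-week figure without any day value. In the text, the alternative-arm rule for an incorrect dose covers cases where "infants enrolled in the alternative schedule group receive a second or third dose of PCV before 40 weeks of age". The standard-arm counterpart is a third dose later than that same age. Table 4 repeats this in three lines under its heading for incorrect doses: "Alternative schedule—2nd dose age <40 weeks", a matching line for the third dose in that arm, and for the other arm "Standard schedule—3rd dose age >40 weeks". Its line for over-age enrolment is also in weeks only: "Age >40 weeks on day of consent".

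The booster is scheduled at 9 months (*Trial design*). The section *Individual-level cohorts* repeats the per-protocol enrolment limit as 273 days, with no week figure.

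**The concern.** The two units in the per-protocol definition cannot both be right, and the wrong one is carried into the rules that decide which doses count as protocol deviations. In the per-protocol section the day value sits beside the week value, so a reader can see the discrepancy. In the deviation rules nothing corrects it.

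Two things are at stake. The first is the deviation table: the alternative arm's count of incorrect doses could include boosters given at the age the schedule asks for. The second depends on programming. If someone coded the week value in the per-protocol definition, boosters in the first week of the window would remove children from the per-protocol cohort in the alternative arm only. That cohort feeds the per-protocol disease and safety comparisons and the exploratory analyses before and after the booster.

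**Working it through.** **Inputs**
- Per-protocol booster window: 273 to 365 days, with the lower limit glossed as 40 weeks (*Vaccination status—per-protocol*).
- Deviation limit for the alternative second dose: below 40 weeks, no days given (*Definition of protocol deviations*, Table 4).
- Deviation limit for the standard third dose: above 40 weeks, no days given (same places).
- Nine months plus two weeks is set at 288 days (*Additional analyses*).

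**Step 1: try to reproduce the plan's 40 weeks**
- Exact weeks: 273 / 7 = 39.0.
- Completed weeks: 39.
- Conversely, 40 × 7 = 280 days, a gap of 280 − 273 = 7 days.
- Only a running-week count gives 40, since day 273 opens the 40th week (39 + 1).

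**Step 2: does the plan count running weeks elsewhere?** It does not. These limits in the neighbouring adherence sections are exact multiples of 7:

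| Days | Weeks stated | Days / 7 | Running week |
|---|---|---|---|
| 112 | 16 | 16.0 | 17 |
| 182 | 26 | 26.0 | 27 |
| 252 | 36 | 36.0 | 37 |
| 294 | 42 | 42.0 | 43 |
| 336 | 48 | 48.0 | 49 |
| 273 | 40 | 39.0 | 40 |

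Table 4 also uses 36 weeks, which the adherence definitions fix at 252 days. A programmer who converts 36 weeks to 252 days in that table would convert 40 weeks to 280 days.

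**Step 3: overlap for the alternative-schedule booster**
- Per-protocol in days: 273 ≤ age ≤ 365.
- Deviation read literally: age < 280.
- Both hold on days 273 to 279, that is 279 − 273 + 1 = 7 days.
- Deviation read as 273 days: age < 273, so the overlap is 0 days.

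**Step 4: where the scheduled age falls.** From the plan's own figure, 9 months = 288 − 14 = 274 days. A calendar calculation gives 9 × 365.25 / 12 = 273.9 days. Either way, a booster given exactly on schedule lies in the 7-day overlap.

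**Step 5: the standard-schedule third dose**
- On the 273-day reading, a deviation begins at day 274.
- On the literal reading, it begins at day 281.
- Days 274 to 280 (7 days) change status between the two readings.

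**Step 6: if the week value were coded in the per-protocol definition.** A two-dose child boosted on days 273 to 279 would leave the per-protocol group. That child would fit none of the SAP's other individual adherence classes for the alternative arm that apply to a child who stays in the area:
- the intention-to-treat vaccination class needs a second dose at 336 days or later;
- incomplete vaccination means one dose only;
- cross-over needs three or four doses.

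**Number of children.** The SAP gives no distribution of booster age, so this cannot be calculated.

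**The case against.** The strongest reply is that the SAP supplies its own conversion. The only place where 40 weeks is paired with days says 273. The cohort definitions repeat 273 days without weeks, and other age limits are also in days. On that reading Table 4 means 273 days and there is no conflict. A rule that calls a booster at the scheduled age incorrect is also unlikely to be what the authors meant.

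This stands as evidence of intent: 273 days throughout is the likely meaning, and per-protocol membership is probably sound. It does not settle the text. The stated equivalence is false, neighbouring limits convert exactly, and the deviation rules never say that their weeks are to be read through another section.

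Several stronger readings are tempting, and the document does not support them:

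- **That Table 4 misses over-age enrolments on any reading.** A reader might set its 40-week enrolment line against the *Eligibility* limits: above 274 days, or above 182 days in the standard arm from 22 August 2019 to 7 February 2020. But the text introducing Table 4 already counts enrolment of infants over the age limit as a deviation. The table line is less complete than its text; the rule itself is not missing.
- **That the standard arm's late third doses go unreported.** On days 274 to 280 they are already outside per-protocol, which requires all three doses by day 152. They are cross-over in the population-level adherence table (Table 3), and also at individual level if more than 152 days after the first dose. Only their place in the deviation count is uncertain.
- **That a child enrolled on day 274, eligible but not per-protocol, is an error.** A per-protocol set may be narrower than eligibility.
- **That the plan's week figures are wrong throughout.** The other loose pairs (152 days as 21 or 22 weeks, 365 as 52, 1826 as 260) are mostly small rounding. Rounding cannot explain 273, an exact multiple of 7.

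**Conclusion.** The point holds in limited form. The per-protocol section twice states a wrong week equivalent, 7 days out, and the deviation rules reuse the wrong figure with nothing to correct it. Read literally, 7 days of booster age in the alternative arm, including the scheduled age, are both per-protocol and incorrect; read as 273 days, none are. For the standard third dose, another 7 days change deviation status between the readings.

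The consequence is for descriptive deviation counts. Per-protocol analyses are affected only on the assumption that weeks, not days, are programmed, and the loss would then fall on one arm. A reader might infer that the trial's main conclusions are at risk. They are not: the primary endpoint and the community carriage endpoint take residents by cluster whatever doses they received, and the secondary radiological pneumonia endpoint uses the intention-to-treat cohort. This is a correction worth making because it removes a contradiction in a rule the trial applies.

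**What to change.** 1. In *Vaccination status—per-protocol*, write 273 days (39 weeks) in both places.
2. In *Definition of protocol deviations* and Table 4, state the dose limits in days on the same cut-off: alternative-schedule second or third dose before 273 days, and standard-schedule third dose after 273 days. This takes 273 days as the intended limit, which the trial team should confirm.
3. Add one sentence saying that per-protocol status and protocol deviations are both derived from age in days.
4. Optionally, replace the 40-week enrolment line in Table 4 with a reference to the age limits under *Eligibility*, as the accompanying text already implies.

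The cost is a few wording changes and a check that the code uses days. No new data are needed, and the enrolment criteria themselves do not change.
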